### Control group

Families allocated to the control group will participate in one psychoeducational session of 2 h, either individually or in a group. This will take place within the first 8 weeks after baseline. The facilitator will be an experienced neuropsychologist, who is not involved with the intervention groups. The content of the 2-h session will be equal for all participants in the control groups. They will receive information about the consequences of a traumatic injury, and how it can affect the entire family. Furthermore, information on normal emotional reactions, both in the acute phase, but also in long term, will be discussed. At the end of the session, the family members will be able to share their experiences, and the facilitator will give them advice about, where to receive more support and/or information. The control groups are offered psychoeducational support as it seems unethical not to offer these families anything because of the promising results from the pilot study in Latin America [42]. The rationale behind offering these families a single psychoeducational session is that they will receive some support, but the support is expected to have a short-term effect and will consequently not affect the results when comparing the two groups (intervention group and control group). If the family intervention turns out to be effective, all families allocated to the control groups will be offered the 8-week family intervention after the study completion.

### Outcomes

The manual-based family intervention for families with TBI or tSCI has not been implemented in Denmark prior to this study. Thus, we are interested in the effect of the family intervention, but also the families’ subjective experiences of participating in the intervention. Consequently both quantitative and qualitative data will be collected.

#### Questionnaires

##### Socio-demographic data

The following information will be collected at baseline (session 1): age, gender, number of years of education, and cause and date of injury. Other socio-demographic characteristics will be collected at all three timepoints, i.e. baseline, post-intervention (8 weeks after baseline) and at 6-month follow up including civil status, family member relationship, duration of relationship, members in the household, employment status, number of weekly hours spent on work or education, comorbidities, medical drug use, social network, and whether they have participated or currently are participating in another therapeutic setting with a psychologist. The patients will also complete questions about rehabilitation, if they still receive support from an occupational or physio therapist, and if they have been hospitalized during the family intervention. Caregivers will complete information on the hours spent on caring/supervising the patient each day.

##### Injury characteristics

The Glasgow Coma Scale [47] and length of PTA [48, 49] will be used as an indicator of injury severity for patients with TBI. The neurological level and severity of the spinal cord lesion will be assessed in patients with tSCI according to the International Standards for Neurological Classification of Spinal Cord Injury, including the American Spinal Injury Association Impairment Scale [50, 51]. The length of stay will be registered for both disease groups.

##### Primary and secondary outcome

The effect of the family intervention will be measured by self-report questionnaires. The outcome measurements are outlined in Table 2 and will be measured at baseline, post-intervention, and at 6-month follow up (Table 2).

**Table 2 Tab2:** Primary and secondary outcome measures

Domain	Assessment	Test tool (outcome measure)	Administered by
Quality of life (QoL)	Generic QoL	Short Form-36 (SF-36) [9, 10, 52, 53]	All participants
	The patient’s disease-specific QoL	QoL after Brain Injury (Qolibri) [54]	Participants with TBI
		International Spinal Cord Injury QoL Basic Data Set [55]	Participants with tSCI
Self-perceived burden	General burden, isolation, disappointment, emotional involvement, environment	Caregiver Burden Scale (CBS) [12, 56]	Caregivers
	Physical, emotional and financial burden	Self-Perceived Burden Scale (SPB) [57]	Participants with TBI or tSCI
Family dynamic	Flexibility	Family Adaptability and Cohesion Evaluation Scales-IV (FACES-IV) [58]	All participants
	Cohesion		
	Communication		
Problem-solving abilities	Confidence	Problem-Solving Inventory (PSI) [59]	All participants
	Personal control		
	Approach-avoidance		
Mental health	Depression	Patient Health Questionnaire-9 (PHQ-9) [60]	All participants
	Anxiety	Generalized Anxiety Disorder-7 (GAD-7) [61]	
	Satisfaction with life	Satisfaction with Life Scale (SWLS) [62]	
Relationship	Relationship to relatives	Relationship Assessment Scale (RAS) [63–65]	All participants if a dyad
Resilience	Resilience and robustness	The Resilience Scale for Adults (RSA) [66]	All participants

All participants in the two groups will complete self-report questionnaires to collect generic QoL data as the primary outcome measurement, and self-perceived burden, family dynamics, problem-solving strategies, mental health, and resilience as secondary outcome measurements. In cases where the family consists of a dyad, e.g. a married couple, mother and daughter etc., rather than several family members, the Relationship Assessment Scale (RAS) [63–65] will be completed as a supplement.

##### Treatment compliance

All participants and the neuropsychologist will complete a measure of compliance. Participants allocated to the intervention group will individually complete the Session Rating Scale (SRS) [67] after each session. The SRS is a paper and pencil four-item scale used to evaluate the individuals’ experience with the relevance of the specific topic of the session, including strengths and weaknesses, and their experience with the neuropsychologist. The neuropsychologist will leave the room during this task. The families will be instructed to put the completed questionnaire in an envelope, consequently the neuropsychologist will be blinded to their answers.

When the 8 sessions are completed, the neuropsychologist will complete an evaluation form, the Therapist Checklist Scale, which evaluates the participants’ attendance [68]. It is a five-item scale, where the neuropsychologist will rate the participants according to their engagement in the intervention, including level of participation, homework assignments, interaction with the other family members and the neuropsychologist, and their ability to use the strategies from each session [68, 69].

#### Semi-structured interviews

The experiences with the manual-based family intervention will be investigated qualitatively by conducting individual semi-structured interviews with 20 families who have finished the 8-week family intervention. The families will be selected based on representativeness of disease (TBI or tSCI), different family structures (e.g. couples, parents with adult children, siblings), and age and gender of the survivor. Qualitative data will be used to analyse, it will be possible to add qualitative data, which will be used to analyse the families’ individual experience of participating in the intervention. The interviews will include the families’ experiences of the structure and content of each session, and the amount and content of homework. Furthermore, the participants will be asked if and how the intervention was meaningful for their specific situation. A research nurse will conduct the interviews within the first 4 weeks after the intervention has been completed will interview the families within the first 4 weeks after the intervention has been completed.

### Sample size

Preliminary statistical power calculations have been carried out to allow us to detect any group effect (intervention versus control in the TBI and tSCI group, respectively) on the primary outcome variable, i.e. generic QoL data assessed by the Short Form-36 (SF-36) [9, 10]. Numbers of participants required in the study were calculated based on the Mental Component Summary (MCS) of the SF-36 [52, 53]. As no studies have been carried out in Denmark using the SF-36 in patients with a traumatic injury, a Norwegian study [70] was used for the sample size calculations. In the Norwegian study, a score of 43.8 (SD 12.5) was reported among patients with moderate to severe TBI. Based on a confidence level of 95%, a power level of 80%, and a significant difference of 5 points between the intervention and control group, it will be necessary to recruit 182 participants to each arm of the trial i.e. the TBI and tSCI arms. To account for a 10% drop-out rate, 400 participants in total must be included.

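### The 182 participants per disease group do not follow from the stated inputs, which need 198 to 200; on those inputs power is about 77%, not 80%

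*Protocol article*

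**What the plan says.** The Sample size section of the protocol article powers the trial for "intervention versus control in the TBI and tSCI group, respectively", so each disease group has to carry its own comparison. The required number was "calculated based on the Mental Component Summary (MCS) of the SF-36". The SD comes from a Norwegian study in which "a score of 43.8 (SD 12.5) was reported among patients with moderate to severe TBI". The target is "a significant difference of 5 points between the intervention and control group", at 95% confidence and 80% power.

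From this the section concludes that "it will be necessary to recruit 182 participants to each arm of the trial i.e. the TBI and tSCI arms". It then adds: "To account for a 10% drop-out rate, 400 participants in total must be included".

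The Randomization section fixes 1:1 allocation within each disease group, so 182 per disease group means 91 intervention and 91 control. The Sample size section mentions no one-sided test, no within-person correlation and no variance reduction from baseline adjustment.

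**The concern.** Every input to a standard two-sample calculation is printed, so the result can be checked directly, and 182 is not what the inputs give. This is the only power justification for the primary outcome, and it applies separately to TBI and to tSCI. If the number is too small for the stated inputs, the risk of missing a true 5-point difference is larger than the stated 20% in each of the two comparisons. The figure also has a practical role: the Trial status section says that enrolment ends once the estimated sample size has been included.

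**Working it through.** **Inputs.** All are from the Sample size section except the last two.
- SD 12.5 and difference 5, so the standardised difference is 5/12.5 = 0.4.
- Power 80%.
- Confidence 95%, read as a two-sided 5% test. Sidedness is not stated, so one-sided is tried as well.
- Allocation 1:1 within disease group (Randomization section).
- Participants treated as independent. This is an assumption here; the printed calculation mentions no adjustment for families.

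**Attempt to reproduce 182.** Per treatment group, n = 2 × (1.960 + 0.842)² × 12.5² / 5² = 98.1, so 99. The exact two-sample t-test gives 99.08, so 100. Per disease group this is 198 or 200. The printed 182 is 8 to 9% lower (16/198 = 8.1%; 18/200 = 9.0%).

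**Other readings of 182.**

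| Reading | Result | Match? |
|---|---|---|
| Two-sided 5%, SD 12.5, difference 5 | 198 to 200 per disease group | no |
| One-sided 5% | 78 per treatment group, 156 per disease group | no |
| 182 per treatment group | about 97% power; 4 × 182 = 728 in total | contradicts 400 |
| SD 12.0, difference 5 (normal formula) | 91 per treatment group, 182 | yes, but SD 12.0 is not stated |
| SD 12.5, difference 5.2 (normal formula) | 182 | yes, but 5.2 is not stated |

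In addition, 200/1.1 = 181.8. It is therefore possible that 200 per disease group was the calculated requirement and that 182 was obtained from it by working backwards. The document does not say.

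**Power at the printed numbers, for a 5-point difference and SD 12.5.**

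| Per treatment group | Where it comes from | Normal | t-test |
|---|---|---|---|
| 91 | 182 per disease group | 77.0% | 76.5% |
| 90 | 400 × 0.9 = 360, over four groups | 76.5% | 76.1% |
| 100 | 400 with no drop-out at all | 80.7% | 80.4% |

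So 400 gives 80% power only if nobody is lost, while the section plans for 10% loss.

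**Difference detectable with 80% power.** 12.5 × √(2/n) × 2.802 gives 5.19 at n = 91 and 5.22 at n = 90, so about 5.2 points.

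**Drop-out step.** Two disease groups of 182 make 364. The printed 400 is consistent with 364 × 1.1 = 400.4. To keep 364 after 10% loss needs 364/0.9 = 404.4, so 405. The gap is 5 participants. Its effect is the step from 91 to 90 per treatment group, about half a power point.

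**Numbers that deliver 80% on the stated inputs.** 396 (normal) to 400 (t-test) evaluable in total. With 10% drop-out: 396/0.9 = 440 and 400/0.9 = 444.4, so 440 to 445.

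**The case against.** The strongest reply is that the calculation describes a simpler analysis than the one planned. The Analytical methods section specifies a repeated-measures ANOVA over three time points, with adjustment for baseline if the groups differ. Its power depends on a within-person correlation that the document does not give. As an assumption only: if baseline were always a covariate, the variance would fall by the factor 1 − r². A correlation of about 0.3 would then bring power back to about 80% at 90 to 91 per treatment group, and 0.5 would give about 87%. A change-score comparison with a correlation below 0.5 would do worse than the simple comparison.

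This stands against one tempting inference, that the trial as analysed will fall short of 80% power. The document does not support that. It does not rescue the printed calculation, though: the Sample size section claims no variance reduction, and baseline adjustment is planned only if a baseline difference is significant, so it cannot be counted on in advance.

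A second reply is that the section calls its calculations preliminary and takes the SD from one sample of patients with TBI, then applies it to tSCI and, as all participants complete the SF-36, to caregivers. A change in SD from 12.5 to 12.0, which is 4%, removes the discrepancy, and the true SD may well be uncertain by more than that. This is fair and limits the weight of the point. It does not make 182 the right answer for 12.5.

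A reader might also take the drop-out step as a second material error or as the cause of the shortfall. It is neither: the loss comes almost entirely from the base figure of 182.

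**Conclusion.** The point holds as an arithmetic error in the text. On the stated inputs 198 to 200 evaluable participants per disease group are needed, not 182. The simple two-group comparison has about 77% power at 91 per treatment group and about 76% at 90, so the stated 80% is 3 to 4 points too high and the false-negative risk is about 23 to 24% instead of 20%.

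This rests on a two-sided 5% test, SD 12.5, 1:1 allocation and independent participants. Correlation within families is a separate matter and adds nothing to the size given here.

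The paragraph should be corrected because it is wrong as written. The shortfall is moderate, and the comparison, the outcome and the conduct of the trial are unaffected. Nor does it follow that enrolment has to rise, since restating the power is enough to make the text true.

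**What to change.** Correct the Sample size paragraph in one of two ways:
- Keep 400 and state that, after 10% loss (90 per treatment group within each disease group), it gives about 76% power for 5 points, or 80% for about 5.2 points, under the stated assumptions.
- If a different SD, difference or variance reduction was actually used, state it and show that it leads to 182.

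In either case, give the number per treatment group within each disease group, state whether the test is two-sided, and allow for drop-out by dividing by 0.9.

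For reference, 80% power on the stated inputs takes 396 to 400 evaluable participants, about 440 to 445 with 10% drop-out. Adopting those figures would mean enrolling 40 to 45 more than the planned 400. The first option needs none; its cost is a text change and a slightly less favourable power statement.

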**Methods:**

The study is an interventional, two-arm, randomized controlled trial. During a 2-year period, a total of 132 families will be included. Participants will be recruited from East-Denmark. Inclusion criteria are (1) TBI or tSCI, (2) ≥ 18 years of age, (3) ≥ 6 months to ≤ 2 years since discharge from hospital, (4) ability to understand and read Danish, (5) cognitive abilities that enable participation, and (6) a minimum of one family member actively involved in the survivor’s life. Exclusion criteria are (1) active substance abuse, (2) aphasia, (3) prior neurologic or psychiatric diagnose, and (4) history of violence. Within each disease group, families will be allocated randomly to participate in an intervention or a control group with a ratio 1:1. The intervention groups receive the family intervention consisting of eight sessions of 90 min duration. Families in the control groups receive 2 h of psychoeducation. All participants complete questionnaires on QoL, self-perceived burden, family dynamics, problem-solving strategies, mental health, and resilience at pre-intervention, post-intervention, and 6-month follow up.

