## Methods

### Trial design

This is a two-arm RCT of a manualized family intervention conducted in two different disease groups: (1) patients with TBI and (2) patients with tSCI, participating with a minimum of one family member actively involved in the patient’s life. The duration of the study is from October 2018 to October 2021 with an inclusion period of 2 years. The trial was developed according to the guidelines for Standard Protocol Items: Recommendations for Interventional Trials (SPIRIT) statement [43] (see Additional file 1 and Fig. 1), and will be reported as stated in the Consolidated Standards of Reporting Trials statement for reporting randomized trials of social and psychological interventions (CONSORT-SPI) [44].

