### Randomization

#### Sequence generation and allocation concealment mechanism

Within each disease group, families will be allocated randomly to the intervention group or the control group with an allocation ratio of 1:1. The Sealed Envelope application will be used to generate random allocation sequences: this is an online software application for randomizing patients into clinical trials [71]. The random allocation sequence will be generated and concealed from the employees in the project. The families will consecutively be allocated to each group. Two arms for the TBI group and two arms for the tSCI group will be created with 66 families in each disease-specific group. The randomization will be conducted in blocks of 22, which increases the likelihood that the intervention groups and the control groups will have the exact same number of participants, even in the case of recruiting fewer participants than expected. When entering the unique family ID number in Sealed Envelope, the application randomizes the family to either the intervention group or the control group.

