## Trial status

This is study protocol version 1.0. Recruitment of participants for the study commenced in September 2018, and the first family was included and participated in session 1 on 17 October 2018. At present, 13 families have been randomly assigned (8 families of a patient with TBI and 5 families of a patient with tSCI): 5 families have been randomized to the intervention group and 8 families have been randomized to the control group; currently, 4 families have participated in the semi-structured interview. The estimated enrollment period, including recruitment and inclusion, is anticipated to be 2 years (October 2020) and will conclude, when the estimated sample size has been included.

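### The sample size counts people but enrolment counts families; the link is an unstated mean of about three per family, and the stated 80% power is not secured.

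*Protocol article*

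**What the plan says.** The Sample size section works in people. Its inputs are an SD of 12.5 on the SF-36 Mental Component Summary and the following: "Based on a confidence level of 95%, a power level of 80%, and a significant difference of 5 points between the intervention and control group". The comparison it powers is intervention against control within the TBI group and within the tSCI group. It arrives at 182 participants for each disease group (which it calls an arm), and then: "To account for a 10% drop-out rate, 400 participants in total must be included".

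Enrolment and randomization work in families. The Abstract says that "a total of 132 families will be included". Sequence generation and allocation concealment mechanism creates two randomized groups per disease, "with 66 families in each disease-specific group", and randomizes by family ID, 1:1.

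The number of people in a family has a floor of two. Trial design has patients "participating with a minimum of one family member actively involved", and Primary and secondary outcome adds a relationship scale for the smallest families: "In cases where the family consists of a dyad, e.g. a married couple". Under Participants, relatives must be adults who understand and read Danish, and those with a prior neurologic or psychiatric diagnosis are excluded. The article gives no expected family size.

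Trial status says that enrolment "will conclude, when the estimated sample size has been included". It does not say whether that size is 132 families or 400 people.

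**The concern.** A count of people and a count of families describe the same trial only through a mean family size. Without that figure, the reader cannot tell whether the family target supports the power claim. If families average fewer than about three, 132 families yield fewer than 400 people, and the comparison within each disease group is weaker than stated. If recruitment instead runs to 400 people, the number of families departs from 66 per disease group. The rule for ending enrolment then has two readings, which stop at different points whenever the mean is not 3.03. At stake is the credibility of the 80% power for the primary outcome, and how a null result in either disease group would be read.

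**Working it through.** **Inputs.** From Sample size: difference 5 points, SD 12.5, 95% confidence, 80% power, 10% drop-out, 182 people per disease group, 400 in total. From the Abstract and the randomization section: 132 families, 66 per disease group, 1:1. From Participants: at least two people per family. Assumed here: a two-sided test (the article does not state sidedness) and, at first, independence of family members.

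**The protocol's own figure.** For two means, n per randomized group = 2 × SD² × (1.960 + 0.842)² / difference² = 2 × 156.25 × 7.849 / 25 = 98.1. This rounds up to 99, or 100 with the t distribution, so 198 to 200 people are needed per disease group. The stated 182 (91 per randomized group) is not reproduced; it gives power of about 77%. A one-sided test would need 156, which does not match either. The drop-out step does follow from 182: 2 × 182 = 364, 364 / 0.9 = 405 and 364 × 1.1 = 401, both close to 400.

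**The implied family size.** 400 / 132 = 3.03 (the same as 200 / 66 in each disease group). For 364 before drop-out it is 364 / 132 = 2.76.

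**Power with 66 families per disease group.** With m people per family, each randomized group has 66 × m / 2 people, multiplied by 0.9 after drop-out. Power is from a two-sample t-test with standardized difference 5 / 12.5 = 0.4.

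| Mean per family | People in all | Per randomized group | Power | Per randomized group after 10% drop-out | Power |
|---|---|---|---|---|---|
| 2 (all dyads) | 264 | 66 | 63% | 59.4 | 58% |
| 2.5 | 330 | 82.5 | 72% | 74.25 | 68% |
| 3 | 396 | 99 | 80% | 89.1 | 76% |
| 3.03 | 400 | 100 | 80% | 90 | 76% |

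With all dyads after drop-out, the difference detectable at 80% power is about 6.5 points instead of 5.

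**Head count at the floor.** 132 × 2 = 264 people, which is 136 (34%) short of 400. Reaching 400 people with dyads alone would take 400 / 2 = 200 families.

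**Within-family correlation.** Families are randomized, so the effective number is the head count divided by 1 + (m − 1) × ICC. The article gives no ICC; 0.1 to 0.5 is an assumed range. Before drop-out, power for three per family runs from about 72% (ICC 0.1) to 50% (ICC 0.5), and for dyads from about 58% to 46%.

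**The case against.** A reader might infer that the two targets contradict each other. They do not: 132 × 3 = 396, close to 400, and the figures look like a plan built on about three people per family. The article condenses a fuller protocol record, and one sentence would supply the assumption. This objection stands against calling the targets impossible to reconcile. It does not supply the missing figure, and the article itself sets out both targets, the floor of two and an end-of-enrolment rule without a unit.

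A reader might also take 58% or 63% as the power the trial will have. That assumes every family is a dyad. The article gives no share of dyads and describes an intervention for the whole family, so this is a lower bound on the independence calculation.

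Nor are dyads the sole reason that 80% is missed. The full 400 less 10% gives only about 76%, because 182 is too few for the stated inputs.

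The independence calculation also exaggerates how much family size matters. Between dyads and three per family the gap is about 17 points at ICC 0, but about 4 to 5 points at ICC 0.5. This stands too, but correlation narrows the gap by lowering both figures.

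Pooling both disease groups would give all dyads about 90% power (87% after drop-out) under independence. Pooling is not the stated analysis: Sample size and Analytical methods both work within each disease group.

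**Conclusion.** The concern holds as an unstated and unsecured assumption, combined with a power claim that the stated inputs do not meet. The people and family targets match only at a mean of 3.03 per family, which no eligibility rule ensures. With 66 families per disease group, power after the planned drop-out is about 58% at the floor of two, 68% at 2.5 and 76% at three. Thus 80% is not reached after drop-out even if the family size is as the totals imply. These figures rest on a 5-point difference, SD 12.5, a two-sided 5% test and independent family members; positive correlation within families would make them lower. The documents do not support the stronger conclusions that the targets are incompatible, that the trial will consist of dyads, or that dyads alone cause the shortfall.

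**What to change.** In Sample size and Trial status, state which unit ends enrolment. The randomized unit, 66 families per disease group, is the natural choice. Keeping 400 people and letting the number of families vary would also remove the ambiguity, but it departs from the planned 66.

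State the assumed mean family size. Replace the fixed 400 with an expected range: 264 people at two per family, 330 at 2.5, 396 at three. The sizes of the 13 families already randomized can be reported alongside, although 8 TBI and 5 tSCI families are thin support for a mean.

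Correct 182, or give the inputs from which it follows. Then restate power or the detectable difference over the range of family size, after 10% drop-out and over a stated range of within-family ICC. A restatement under independence and before drop-out alone would still show about 80% at three per family, and so would not settle the point.

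The cost is protocol wording and a less favourable stated power. No extra families, visits or procedures are required.
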